## GLOSSARY OF ABBREVIATIONS AND TECHNICAL TERMS

|             |                                                                     |
|-------------|---------------------------------------------------------------------|
| AKI         | Acute Kidney Injury                                                 |
| APS         | Acute Kidney injury Prediction Score                                |
| AVPU        | level of consciousness – Alert/ responds to voice/Pain/Unresponsive |
| CCF         | congestive cardiac failure                                          |
| CKD         | Chronic Kidney Disease                                              |
| DM          | Diabetes                                                            |
| EWS         | Early warning system                                                |
| eGFR        | Estimated glomerular filtration rate – measure of kidney function   |
| LOS         | Length of stay                                                      |
| Patientrack | WSHT electronic observation system                                  |
| PAS         | Patient administration system                                       |
| RR          | Respiratory rate                                                    |
| Tachypnoea  | Raised breaths                                                      |
| Tachycardia | Raised number of heart beats                                        |
| WSHT        | Western Sussex Hospitals NHS Trust                                  |

## KEYWORDS

Acute Kidney injury, Alerting tool

## STUDY SUMMARY

|                         |                                                                                                                                                                                                                                                                                                                                                                                                                                       |
|-------------------------|---------------------------------------------------------------------------------------------------------------------------------------------------------------------------------------------------------------------------------------------------------------------------------------------------------------------------------------------------------------------------------------------------------------------------------------|
| TITLE            | Electronic alerting tool to help prevent acute kidney injury                                                                                                                                                                                                                                                                                                                                                                   |
| DESIGN           | Observational Cohort Study                                                                                                                                                                                                                                                                                                                                                                                                            |
| AIMS             | 

1. Externally validate an Acute Kidney injury Prediction Score (APS).

2. Identify patients who are at risk of developing Acute Kidney Injury following hospital admission to highlight the need for closer monitoring, allow preventative measures to be put in place and thus improve outcomes

                                                                               |
| OUTCOME MEASURES | 

• Incidence of Acute Kidney Injury (AKI)

• Magnitude of acute deterioration in Creatinine, eGFR

• Compliance with AKI checklist

• Mortality

• Morbidity – secondary complications including other organ failures

• Length of stay

• Requirement for renal replacement therapies

• Requirement for escalation to critical care

 |
| POPULATION       | Patients admitted to WSHT Acute Medical Units & Becket Ward                                                                                                                                                                                                                                                                                                                                                                           |
| ELIGIBILITY      | All patients over the age of 18 admitted to the Acute medical Units and Becket Ward in WSHT                                                                                                                                                                                                                                                                                                                                           |
| DURATION         | 24 months                                                                                                                                                                                                                                                                                                                                                                                                                             |

## 1. INTRODUCTION

### 1.1 BACKGROUND

Acute kidney injury (AKI) is common in hospital in patients with a reported incidence of between 10 – 20% but can be as high as 70% in the critically ill. Much of the early data examining the outcome of patients with AKI focused on the critically ill but increasingly, evidence is accruing which has highlighted the fact that patients with AKI regardless of clinical setting have worse outcomes. Importantly, even small changes in renal function have been shown to be associated with significant increases in mortality. This is reflected not only in terms of mortality risk but also an increase in the development of chronic kidney disease with its associated complications.

In 2009, The National Confidential Enquiry into Patient Outcome and Death (NCEPOD) published its report “Adding insult to injury”, which examined the care of patients who had died in hospital with a primary diagnosis of acute kidney injury (AKI) or acute renal failure recorded on their death certificate. The overall findings were very critical of the care delivered to patients with renal impairment. Within the report, the group made some key recommendations regarding the admission and assessment for presence of AKI, the investigation of established AKI and its subsequent management. This particular study highlighted that in over 40% of cases there was deemed to be an unacceptable delay in diagnosing AKI and in 20% of cases the AKI was thought to be both predictable and avoidable. Parallels can be drawn with similar reports on the care of acute medical emergencies which highlighted the need for improved recognition of the deteriorating patient. This has led to the use of track and trigger systems in tandem with a physiological warning score.

Several studies have tried to address this problem. In particular electronic systems have been studied where automatic alert warnings of patients with a rise in serum creatinine have been generated. Such alert systems highlight a rise in creatinine after insult but do not inform as to the patients at risk of developing AKI following admission. The risk for development of AKI has been studied in specific patient groups predominantly in surgical and burns patients. An AKI risk index for patients undergoing general surgery has been described where patients developing a rise in serum creatinine of over 177µmol/l (>2mg/dL) or AKI necessitating dialysis were found to have 11 independent preoperative predictors of AKI. In keeping with other work they also demonstrated an 8-fold increase in mortality in patients who developed AKI. However, few attempts have been made to try to identify patients at risk of developing AKI when admitted to hospital as acute medical emergencies outside critical care. This is of particular relevance in that the majority of admissions to critical care with AKI are medical admissions. Attempts have been made to utilise electronic health records to produce a risk stratification model but this is not easily applied at the bedside and does not employ any physiological parameters.

We have developed a simple, robust and practical scoring system utilising both physiological measurements, biochemical parameters and known co-morbidities that is easily calculable

and can identify patients at risk of developing AKI following hospital admission. We have named this the **Acute Kidney injury Prediction Score (APS)**. Furthermore we have developed this into an automated electronic AKI prediction & identification tool utilising the hospital Patient Administration System (PAS), pathology database & Patienttrack physiological Early Warning System (EWS) to deliver near real-time alerts to nursing and medical staff. The alert can trigger an automated e-mail to the patient's consultant and will advise on a care bundle which can be individualised for the patient.

### **Research Question/ Main Aims:**

Phase 1 – is the APS externally valid? We will assess this by retrospective external validation of the score on the Chichester site.

Phase 2 - can the use of an electronic prediction & identification alerting tool to deliver an individualised care bundle for hospital in-patients at risk of or with confirmed AKI reduce:

1. The incidence of AKI in those patients 'at risk'
2. The harm (mortality, morbidity, Length of stay (LOS)) associated with failure to recognise those patients with confirmed AKI

### **Outcomes/ Analysis:**

Phase 1 – external validation of the APS to predict the development of Acute Kidney Injury on another hospital site

Phase 2 – can the introduction of an alert impact on:

- Incidence of AKI
- Magnitude of acute deterioration in Creatinine and estimated glomerular filtration rate (eGFR)
- Mortality
- Morbidity – secondary complications including other organ failures
- LOS
- Requirement for renal replacement therapies
- Requirement for escalation to critical care

### **Main benefits & potential impact to NHS:**

1. Health benefits immediate & projected medium to longer term
2. Cost-benefit analysis

The trial will be conducted in compliance with the principles of the Declaration of Helsinki 6th revision, the principles of ICH-GCP and all applicable regulatory requirements. The protocol is to be submitted for approval by a Research Ethics Committee.

## **1.2 RATIONALE FOR CURRENT STUDY**

As the 2009 NCEPOD report highlighted, AKI is a common medical complication that is often diagnosed late and in many cases predictable and avoidable. From our own Worthing Hospital Audit data over six months through the Acute Medical Unit, AKI on admission to hospital had a prevalence of 11%. In addition, 7% of patients subsequently developed AKI during admission. Overall mortality for this combined group of patients with AKI was 19-20%.

Our innovative scoring system - the **Acute Kidney injury Prediction Score (APS)** - utilising physiological measurements, biochemical parameters and known co-morbidities can identify patients at risk of developing AKI following hospital admission. This can then deliver near real-time alerts to nursing and medical staff and will advise on a care bundle.

We would like to retrospectively externally validate the scoring system at another site to add methodological rigor. We will use two parallel interrupted time-series studies, on the Worthing & Chichester sites at WSHT, with segmented linear regression analysis in order to evaluate the longitudinal effect of intervention (use of the score and subsequent alert) and controls for trends in outcome.

## **2. STUDY OBJECTIVES**

### **2.1 Trial objectives**

1. Retrospectively externally validate the APS
2. Can the use of an electronic prediction & identification alerting tool to deliver an individualised care bundle for hospital in-patients at risk of or with confirmed AKI reduce:
  - a. The incidence of AKI in those patients 'at risk'
  - b. The harm (mortality, morbidity, LOS) associated with failure to recognise those patients with confirmed AKI

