### **2.3 Trial statistics**

#### **Statistical methods**

#### **Sample size for original study**

Worthing Audit data Feb 2010-July 2010: 3400 patients admitted through the Acute Medical Unit:

n= 1746 with a pre-admission creatinine (51.3%)

Of this cohort n=184 had AKI on admission (11%) 1561 (88%) did not

Of remaining group n=1219 did not develop AKI

N=95 (7%) developed AKI during admission

Figure 1: Patient Flow Chart

[figure not shown]

Figure 1 – flow chart for initial derivation of Acute kidney injury physiological scoring (APS) system. Based on 6 months data and a cohort of 1746 patients who had a recent creatinine result.

|                              | Incidence | Hospital mortality |
|------------------------------|-----------|--------------------|
| AKI on admission to hospital | 11%       | 19%                |
| Hospital acquired AKI        | 7%        | 20%                |

The initial retrospective validation on the St Richard's site will involve a similar number of patients to enable statistical significance in terms of incidence of acute kidney injury to be assessed. A similar number of patients will then be assessed prospectively once the Acute kidney injury alert is introduced onto the Worthing site to allow comparisons between the two sites.

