### Biochemistry Results – Real time Creatinine

[figure not shown]

(Abbreviations: AVPU level of consciousness – Alert/Vocal/Pain/Unresponsive; CCF – congestive cardiac failure; DM – Diabetes; RR – Respiratory rate)

Results will be displayed within the patient chart as a traffic light system (No AKI, At risk, Confirmed AKI). If the patient displays 'At risk' or 'Confirmed AKI' then clicking over the traffic light key will take the clinician to a new screen displaying the Creatinine results graphically & a checklist for AKI. An automated AKI alert will be also sent at 0100 each day to the responsible Doctor with a 'read receipt' to acknowledge that the e-mail information has been received. All patients 'at risk' or 'confirmed AKI' will also appear on the AKI Hospital Patient List which can be accessed by the medical staff, Outreach staff & Renal team. This is displayed pictorially on the following page:

Main Patienttrack frontpage

[figure not shown]

Patient Chart

[figure not shown][figure not shown]

CLICK  
INTO

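### Objective 2b judges mortality, morbidity and length of stay in confirmed AKI, a group whose membership the alert is meant to change, so a before/after comparison within it could be distorted by case mix

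*Protocol*

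**What the plan says.** Protocol Section 2.1 sets two effects for one tool. The first, 2a, is to reduce "The incidence of AKI in those patients 'at risk". The second, 2b, is to reduce "The harm (mortality, morbidity, LOS) associated with failure to recognise those patients with confirmed AKI". The research question in Section 1.1 repeats the pair, with 2b worded as "The harm (mortality, morbidity, Length of stay (LOS)) associated with failure to recognise those patients with confirmed AKI".

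The same traffic light and checklist serve both groups (Section 3): "If the patient displays 'At risk' or 'Confirmed AKI' then clicking over the traffic light key will take the clinician to a new screen".

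The only baseline mortality figures are conditional on AKI. Section 1.2 says "Overall mortality for this combined group of patients with AKI was 19-20" per cent. The audit table in Section 2.3 gives 19% for AKI on admission and 20% for hospital-acquired AKI. The matching counts are "Of this cohort n=184 had AKI on admission (11%) 1561 (88%) did not" and "N=95 (7%) developed AKI during admission".

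The outcome lists in the Study Summary, in Outcomes/Analysis (Section 1.1) and in Section 3.1 name mortality, morbidity and length of stay without a population. Section 3 defines the cohort as emergency medical admissions staying at least one night. Section 7 names no population for these outcomes.

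**The concern.** Objective 2a is meant to change who has AKI. Objective 2b then compares outcomes among those who have it, before and after the alert. If 2a succeeds, some patients who would have counted as AKI cases before the alert do not count after it. The two sets of AKI patients are then no longer alike, and a difference in their mortality mixes the effect of recognising AKI with a change in case mix that the alert itself produced.

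The planned design does not separate the two. Segmented regression allows for underlying trends, and the control site allows for changes common to both hospitals. A case-mix change that begins at the site and on the date where the alert goes live looks the same as an intervention effect.

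At stake is the reading of 2b: a real benefit could be hidden or exaggerated, or harm inferred when no patient fared worse.

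**Working it through.** **Inputs from the protocol (Section 2.3 audit):** 184 patients with AKI on admission, mortality 19%; 95 with hospital-acquired AKI, mortality 20%.

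**Reproducing the stated figure.** Deaths: 0.19 × 184 + 0.20 × 95 = 34.96 + 19.00 = 53.96. Combined mortality: 53.96/279 = 19.3%, which agrees with the stated 19-20%. Hospital-acquired cases are 95/279 = 34% of all AKI. The other 66% have AKI on arrival, which an in-hospital alert cannot prevent.

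**Assumptions (not in the documents).** A share f of the 95 hospital-acquired cases is prevented. Those patients would have had mortality m as AKI cases. Nothing changes for anyone else.

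**Formulas**, with k = 95f:
- hospital-acquired AKI: (19 − k·m)/(95 − k)
- all AKI: (53.96 − k·m)/(279 − k)

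| f | m | Hospital-acquired AKI | All AKI |
|---|---|---|---|
| none | – | 19/95 = 20.0% | 53.96/279 = 19.3% |
| 10% | 5% | 18.525/85.5 = 21.7% | 53.485/269.5 = 19.8% |
| 20% | 0% | 19/76 = 25.0% | 53.96/260 = 20.8% |
| 20% | 5% | 18.05/76 = 23.8% | 53.01/260 = 20.4% |
| 20% | 20% | 15.2/76 = 20.0% | 50.16/260 = 19.3% |
| 20% | 30% | 13.3/76 = 17.5% | 48.26/260 = 18.6% |
| 30% | 0% | 19/66.5 = 28.6% | 53.96/250.5 = 21.5% |
| 30% | 5% | 17.575/66.5 = 26.4% | 52.535/250.5 = 21.0% |
| 30% | 20% | 13.3/66.5 = 20.0% | 48.26/250.5 = 19.3% |
| 30% | 30% | 10.45/66.5 = 15.7% | 45.41/250.5 = 18.1% |

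The sign turns on whether m is below or above the group average. At m = 20% nothing moves in hospital-acquired AKI; above that, AKI mortality falls without any benefit to the remaining patients.

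**What a shift could mask.** At f = 30% and m = 5%, a true relative mortality reduction in the remaining cases of 1 − 0.200/0.264 = 24% (hospital-acquired), or 1 − 0.193/0.210 = 8% (all AKI), would leave observed mortality unchanged.

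**An effect that could oppose it.** The Section 3 checklist calls for daily creatinine, so the alert may also bring extra mild cases to light. At f = 30% and m = 5%, adding 30 such cases at 5% mortality (assumption) gives (17.575 + 1.5)/(66.5 + 30) = 19.8% and (52.535 + 1.5)/(250.5 + 30) = 19.3%. These are close to the starting values.

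**The case against.** The strongest reply is that the protocol does not fix the analysis population. Objective 2b is a one-line aim, the outcome lists do not restrict mortality or length of stay to AKI patients, and the cohort is all eligible admissions. An all-admissions series would fit the text as written, and a statistical analysis plan that is not shown may specify it. This stands as a limit on the point. It does not remove it, because the wording of the objective points to confirmed AKI and no passage commits to anything else.

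A reader might go further and infer that the better the alert prevents AKI, the worse it must look on mortality. The documents do not support that. It requires the prevented cases to be low-risk, and no mortality by AKI severity or preventability is given. Some of the text points the other way: patients are flagged on age, comorbidity, respiratory rate and consciousness, and Section 1.1 says that even small changes in renal function go with higher mortality. Extra testing makes the net direction less certain still.

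A reader might also translate the shift into lost power from a two-proportion test on 279 cases. That would not describe this study. The plan is segmented regression with a concurrent site, and the 279 are audit cases that the protocol does not name as the pre-alert comparator.

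Three further replies have some force:
- The pooled shift is small, because two thirds of AKI cases cannot be prevented.
- The audit already reports admission and hospital-acquired AKI separately, and incidence is listed beside mortality, so a change in composition might be noticed. Noticing it would not correct the comparison.
- No figure can be given for length of stay or morbidity. A sicker group need not stay longer, since early deaths shorten stay. For these outcomes the argument is structural only.

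**Conclusion.** The point holds as a structural weakness of uncertain direction. Objective 2b, read as worded, conditions on a group whose membership the same alert is meant to change, and neither the time series nor the Chichester control removes the resulting case-mix difference.

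If 20-30% of hospital-acquired cases were prevented, and the prevented cases' mortality lay between 0% and 30%, mortality in hospital-acquired AKI could read anywhere from about 16% to 29% against 20%, with no change in the remaining patients' outcomes. For all confirmed AKI, the group that 2b names, the range is about 18.1% to 21.5% against 19.3%, or roughly one to two points either way. Both the prevented share and the mortality of the prevented cases are assumptions. Extra creatinine testing after the alert would add a further shift of unknown size.

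**What to change.** State in Sections 2.1 and 3.1, and repeat in the Section 1.1 research question, that objective 2b is assessed in:

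1. patients whose AKI is already present on the admission creatinine, for mortality, morbidity and length of stay; and
2. all eligible admissions, for in-hospital mortality and length of stay.

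Report outcomes within hospital-acquired AKI as descriptive only, not as evidence for or against the alert.

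The first group still tests recognition of confirmed AKI and held 184 of the 279 audit cases (66%). The second captures the net effect of prevention and recognition together.

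This is a wording change that relies on the pathology and patient administration databases already being extracted. Its cost is that hospital-acquired AKI is lost as a separate test and the all-admissions analysis dilutes any effect confined to AKI patients. The audit recorded 279 AKI cases among 1,746 patients with a pre-admission creatinine (279/1,746 = 16%).

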### **2.2 Trial design**

Initial retrospective external validation of the APS on the Chichester site.

2 parallel interrupted time-series design studies, on the Worthing & Chichester sites at WSHT, with segmented linear regression analysis in order to evaluate the longitudinal effect of intervention & controls for trends in outcome.

An in-patient episode will capture data from all these databases and this data will be transferred to an excel spreadsheet before anonymisation.

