### 3. STUDY DESIGN

2 parallel interrupted time-series design studies, on the Worthing & Chichester sites at WSHT, with segmented linear regression analysis in order to evaluate the longitudinal effect of intervention & controls for trends in outcome.

Initially (Phase 1) we will retrospectively review both sites to validate the score. Using the Chichester site this will add external validity to the APS score.

The alert will then be instituted (Phase 2) at the Worthing site during which time both sites will be monitored for the incidence of Acute kidney injury and adherence to the Patienttrack Assessment Pack at the Worthing site. After interim analysis, the plan will then be to roll-out the alert to the Chichester site and further analyses will then be performed.

Worthing and Chichester are relatively close geographically and demographics are similar making the use of the Chichester site as the initial 'control' arm methodologically sound. If there are significant differences in the two populations in terms of AKI incidence and outcomes, they will be picked up in the initial Phase 1 part of the study

Duration: 24 months

Cohort: All medical patients admitted as emergencies to WSHT two sites Acute Medical Units (AMU) and Becket ward and spend at least one night as an in-patient.

**Baseline data collection:** data will be retrieved from the Patienttrack, Pathology & PAS databases relevant to the 'AKI Patienttrack Assessment Pack'. This data will be transferred to an excel spreadsheet and then anonymised. This data will be stored on the WSHT server & only hospital password protected computers will be able to access this data. Anonymised data for mathematical & statistical analysis will be transferred by password protected & encrypted memory sticks or secure NHS e-mail.

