**Introduction of 'AKI Patienttrack Assessment Pack' to WSHT:** every night PAS will be searched for relevant AKI score diagnosis on every new admission within the last 24hrs & this will be fed into the 'AKI' algorithm. Biochemistry will similarly be searched for the worst eGFR in the last 6/12 to identify the diagnosis Chronic kidney disease (CKD) for the AKI score. RR & AVPU will be fed directly from Patienttrack into the algorithm. Therefore we will be able to identify those patients 'at risk of AKI' who have been admitted within the last 24 hours & this will be displayed using a traffic light system on the patient chart within the AKI Patienttrack Assessment Pack. In addition real time Creatinine results will be fed into the AKI Patienttrack Assessment Pack to highlight 'confirmed AKI' using the same traffic light system. This is demonstrated pictorially below:

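### The stated Phase 2 model handles gradual drift and changes common to both sites, but not an abrupt case-mix change at one site around alert go-live, although the predictors needed to adjust for it are already extracted

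*Protocol*

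**What the plan says.** Protocol sections 1.2, 2.2 and 3 each name the same Phase 2 method: two parallel interrupted time series analysed by "segmented linear regression analysis in order to evaluate the longitudinal effect of intervention & controls for trends in outcome". Section 1.2 describes the aim as to "evaluate the longitudinal effect of intervention (use of the score and subsequent alert) and controls for trends in outcome". Logistic regression appears only in section 7, where it serves to find predictors of AKI and to re-evaluate the score.

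Comparability of the patients rests on three statements:

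- Section 3 says that "Worthing and Chichester are relatively close geographically and demographics are similar" and draws its justification for the comparison from this, "making the use of the Chichester site as the initial 'control' arm methodologically sound".
- While only Worthing has the alert, "both sites will be monitored for the incidence of Acute kidney injury". Section 2.3 gives the purpose of the prospective Worthing cohort as "to allow comparisons between the two sites".
- On differences between the sites, section 3 relies on the retrospective first phase to reveal them: "If there are significant differences in the two populations in terms of AKI incidence and outcomes, they will be picked up in the initial Phase".

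Section 3 also lists the inputs to the risk algorithm. Age and coded liver failure, heart failure and diabetes come from the patient administration system, and CKD from the worst eGFR of the previous six months. For the remaining two, "RR & AVPU will be fed directly from Patienttrack into the algorithm". Data relevant to the assessment pack are retrieved both at baseline and after its introduction.

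**The concern.** Phase 2 compares different patients before and after go-live, and between two hospitals, without randomisation. The study's premise is that age, the listed comorbidities, respiratory rate and consciousness level predict AKI. If the mix of these changes suddenly at one site close to go-live, for instance through a change in which patients reach the unit, the outcome series steps for a reason unrelated to the alert. A trend term cannot represent a step, and the other site does not share it, so it enters the estimated level change in full. The Phase 1 check looks at baseline only: it cannot see a later change, and the protocol does not say what follows if a difference is found. At stake is the size, and possibly the sign, of the reported effect on AKI incidence and mortality. The variables that would reduce this risk are extracted anyway to run the alert.

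**Working it through.** **Baseline from the protocol (section 2.3).** 1219 patients did not develop AKI in hospital and 95 did: 95/(1219 + 95) = 95/1314 = 7.23%, which reproduces the stated 7%. The audit covered six months, so 1314/6 = 219 patients per month. An alert effect of 20% relative, which is an assumption because the protocol states no target, equals 0.20 × 7.23 = 1.45 points.

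**Size of a case-mix shift.** Let the score be standard normal with slope d = √2·z(AUC) on the logit scale, and solve the intercept so that average risk is 7.23%. Then move the mean score at one site and recompute the rate.

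| Assumed AUC | Rate after 0.1 SD | Change (points) | Share of 1.45 | Change after 0.2 SD |
|---|---|---|---|---|
| 0.65 | 7.60% | 0.37 | 25% | 0.75 |
| 0.70 | 7.72% | 0.49 | 34% | 1.01 |
| 0.75 | 7.85% | 0.62 | 43% | 1.28 |
| 0.80 | 7.97% | 0.74 | 51% | 1.55 |

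**Which changes get through.** Segmented least squares was simulated on 24 monthly points with the break at month 12 and 219 patients per month. It assumed 30% of patients at high risk, a risk ratio of 3, and 4000 runs.

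| Scenario | Mean level change (points) | Rejections at 5% |
|---|---|---|
| No shift, no alert effect | 0.01 | 4.9% |
| Gradual 10-point drift in high-risk share | 0.02 | 4.9% |
| 10-point step fall at both sites, Chichester subtracted | -0.05 | 4.7% |
| 10-point step fall at Worthing only, single series | -0.91 | 9.0% |
| 10-point step fall at Worthing only, Chichester subtracted | -0.95 | 7.4% |
| True 20% reduction, no shift | -1.47 | 17.1% |
| True 20% reduction, 10-point rise at Worthing | -0.74 | 7.6% |

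The arithmetic agrees. Low-stratum risk is 7.23/(0.7 + 0.3 × 3) = 4.52%, and a 10-point shift moves the rate by 0.10 × (3 - 1) × 4.52 = 0.90 points.

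**Type I error at the planned size.** Section 2.3 plans a number similar to the audit, so take n = 1314 per site-period in a two-site before/after contrast. Let δ be the log odds ratio of the shifted rate p₁ against p₀ = 7.23%, with SE = √[3/(n·p₀(1-p₀)) + 1/(n·p₁(1-p₁))]. The rejection rate is Φ(δ/SE - 1.96) + Φ(-δ/SE - 1.96), taking the 0.05 level of section 7 as two-sided. At AUC 0.70 and 0.1 SD the odds ratio is 1.074, SE 0.211, δ/SE 0.34, and the rate 6.3%. At AUC 0.75 it is about 7%. For 0.2 SD the two figures are 10.4% and 13.5%.

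**Effect of adjustment.** In simulated patient-level two-site contrasts (12 + 12 months, 219 per site-month, no alert effect, 600 runs, AUC 0.70 to 0.75), a 0.2 SD shift gave an unadjusted odds ratio of 1.15 to 1.19. With the score as covariate it was 1.00, and the SE of the log odds ratio was 2 to 4% larger.

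**The case against.** The strongest reply is that covariate lists usually belong in the statistical analysis plan, which is not shown, and that the protocol nowhere rules out adjustment. That stands as far as it goes: an unseen plan may already name covariates. But the protocol does more than stay silent. It chooses the model in three places and defends the comparison by similarity of the sites and a baseline check, and those do not cover a later change at one site.

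A reader might infer several stronger things that the documents do not support.

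- *That only time trend is controlled.* Chichester is a concurrent control, and in the simulation it removes a step common to both sites.
- *That every predictor is held for every admission.* CKD needs an eGFR from the previous six months, and in the audit 1746 of 3400 (51.3%) had a pre-admission creatinine.
- *That the planned regression could not use case-mix data.* The protocol does not say that the data will be aggregated, and an aggregated model can take the monthly high-risk share. In the simulation this cut the bias of the single Worthing series to 0.02 points, although the SE of the level change rose from 1.4 to 2.0 points.

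Objective 2a concerns AKI in patients flagged as at risk, a group that the score itself defines. If these are the top 20 to 40% of scores (an assumption), a 0.1 SD shift at AUC 0.70 to 0.75 changes incidence within the group by 1.6 to 3.1% relative, against 6.8 to 8.5% in the whole cohort. The whole-cohort figures therefore overstate the problem for that objective. They remain relevant because the outcome list in section 3.1 gives AKI incidence without that restriction.

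**Conclusion.** The point holds in a limited form. As stated, the Phase 2 analysis is exposed to an abrupt case-mix change at one site around go-live, and to little else of this kind. Under assumed AUCs of 0.65 to 0.80, a 0.1 SD shift would create or hide about 0.4 to 0.7 points of AKI incidence, or 25 to 51% of an assumed 20% relative effect. The AUC, the shift and the effect size are all assumptions, and nothing in the protocol says that such a change is expected.

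It would be tempting to add that the alert is tested well above the stated 5% level. At about 1314 patients per site-period the documents do not bear that out for a small shift: the rate is about 6 to 7% for 0.1 SD, and 10 to 14% only for 0.2 SD (AUC 0.70 to 0.75). The main harm is a distorted estimate. This should be corrected because the remedy is cheap, but it does not invalidate the design.

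**What to change.** For the yes/no outcomes, state a patient-level segmented logistic model with site, time, post-alert level and slope, and the contrast of these changes between the sites. Adjust it for the score inputs, each measured before the alert: age, heart failure, diabetes, liver failure, first recorded respiratory rate and AVPU, and CKD from pre-admission eGFR with a category for missing eGFR. Keep the unadjusted series as a sensitivity analysis.

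Run the same model on AKI already present on admission, which made up 184 of 184 + 95 = 279 audit cases (66%). The alert cannot act before admission, so a step there would point to a change in case mix or laboratory practice.

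The change needs wording and a little more analysis, with no extra patients or tests. Its costs are an SE about 2 to 4% larger, rules for missing eGFR, respiratory rate and AVPU, and possible drift in diagnosis coding, which adjustment would carry into the estimate.
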